### Statistical analyses

#### **
*Primary outcome: sample size estimation*
**

The primary outcome is thyroid-related quality of life during 12 months’ intervention, as measured by a composite score from the ThyPRO questionnaire. Sample size estimation is based on this outcome.

The trial should be sufficiently powered to identify a difference between the intervention and the control group of four points on the 0 to 100 ThyPRO composite scale, corresponding to a small to moderate effect. In previously obtained data, the standard deviation of ThyPRO-scores (sigma level) was 20 points [14]. With a correlation between observations on the same participant of 0.50, and a power of 80% and a type I error probability (two-sided α level) of 0.05, a sample size of 236 experimental participants and 236 control participants is required. The sample size estimate is based on a design with five repeated measurements having a compound symmetry covariance structure [51].

#### **
*Secondary outcomes: power estimation*
**

Power calculations are based on serum TPO-Ab concentrations and LT4 dosage. Standard deviations used for power calculations were extracted from unpublished data in a study population of approximately 200 AIT patients from Copenhagen and Odense University Hospitals receiving LT4 treatment [14].

#### **
*Serum TPO-Ab concentration*
**

While a previous study has linked TPO-Ab positivity in hypothyroid patients to impaired HRQL [20], we have not found conclusive evidence in the literature that the level of serum TPO-Ab among participants in this trial, that is, AIT patients with serum TPO-Ab concentration ≥100 IU/ml, has clinical implications. The power estimate is based on a design with three repeated measurements having a compound symmetry covariance structure, with a standard deviation (σ level) of 535 IU/ml (unpublished data) [14], a correlation between observations on the same participant of 0.50, and a type I error probability (two-sided α level) of 0.05. Under these circumstances, a difference in serum TPO-Ab levels of 138 IU/ml between the experimental and control group can be identified with 80% power. We find the power of the trial to assess effect on serum TPO-Ab concentrations acceptable.

#### **
*LT4 dosage*
**

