Analyses will be performed using SAS (SAS Institute Inc. ©, Cary, NC, USA), version 9.3 or later. All analyses will be intention-to-treat analyses performed blinded with the two intervention groups concealed as, for example, ‘A’ and ‘B’. Significance tests will be at the 5% level and two-sided. Table 2 shows, for each outcome, its priority, when it will be measured, the mathematical type of measure, and the analytical procedure to be used when analyzing the outcome values. The analytical procedures and handling of missing values are described next.

**Table 2 T2:** Outcome measures

**Outcome (priority)**	**Times of measurements**	**Mathematical type of quantity (analytical category)**
ThyPRO composite scale score (P)	Time sequence of six measurements^a^	Numerical (1 + 2)
ThyPRO hypothyroid symptoms (S)	Time sequence of six measurements^a^	Numerical (1 + 2)
ThyPRO goitre symptoms (S)	Time sequence of six measurements^a^	Numerical (1 + 2)
LT4 dosage (S)	Time sequence of four measurements^b^	Numerical (1 + 2)
Serum TPO-Ab (S)	Time sequence of four measurements^b^	Numerical (1 + 2)
Serum FT3/FT4 Ratio (S)	Time sequence of four measurements^b^	Numerical (1 + 2)
Plasma selenium (S)	Time sequence of four measurements^b^	Numerical (1 + 2)
Biomarkers of immunology and oxidative stress (S)	Time sequence of four measurements^b^	Numerical (1 + 2)
Adverse reactions (S)	End of trial	Rate (3)
Serious adverse events (S)	End of trial	Rate (3)

Outcomes with priorities, times of measurement and mathematical types of quantity with analytical categories. P, primary outcome measure; S, secondary outcome measure. Analytical categories 1 to 3 are defined in the main text. ^a^, includes five measurements relative to the reference time (6 weeks, 3 months, 6 months, 12 months and 18 months after randomization); ^b^, includes three measurements relative to the reference time (3 months, 12 months and 18 months after randomization).

#### **
*Analytical procedures*
**

Depending on the specific analytical category of each outcome measure, one or two of three types of regression analyses will be applied (Table 2).

#### **
*Analytical categories*
**

*Type 1* includes a continuous outcome measure (*y*) measured 3 to 6 times at 6 weeks, 3, 6, 12 or 18 months after randomization. It is viewed as a linear function of time (*t*). The model is:

*y* = *a* + *b***I* + *c***t* + *d***I***t*

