Depending on the mean value structure in the two groups, this model may be enhanced to include a second- or third-degree polynomial. *I* is the intervention indicator, and *a*, *b*, *c* and *d* are the coefficients of the regression equation. A mixed model with repeated measures will be used. An unstructured covariance matrix will be used. In the case of lack of convergence, the following covariance structures will be tried in the specified order: the spatial power law and the compound symmetric.

*Type 2* includes a single continuous outcome measure. The general linear univariate model will be used. As a sensitivity analysis, a nonparametric test (Mann Whitney) will be conducted and the result discussed.

*Type 3* includes a count of events within a specified period of counting as outcome measure. The generalized linear model will be used with the Poisson distribution, link = log and log (period) as offset. As a sensitivity analysis a nonparametric test (Mann Whitney) is conducted to compare the distributions of rates between the groups and the result discussed.

#### **
*Missing values*
**

If the distributions of the primary outcome measure differ significantly between the two intervention groups, multiple imputations (MI) will be used to replace missing data with substituted values using SAS version 9.3 or later. In the MI analysis, the model variables and additional variables significantly related to the variables with missing values of these variables will be used. Ten imputed data sets will be produced.

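### Baseline ThyPRO is collected, but the stated primary model gives it no efficient role; adjusting for it would add power at almost no cost, by an amount that depends on the contrast tested

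*Protocol article*

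**What the plan says.** Table 1 of the protocol article schedules ThyPRO at inclusion and at five later times. Under Analytical categories, the Type 1 outcome is modelled over time ("It is viewed as a linear function of time") as y = a + b*I + c*t + d*I*t, where I is the arm and a to d "are the coefficients of the regression equation". The text allows higher-degree polynomials in time and lists fallback covariance structures. It mentions no baseline score. For Type 2 it says only: "The general linear univariate model will be used".

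It is unclear whether baseline is itself a value of y. Table 2 gives ThyPRO a sequence of six values, and its footnote says that this "includes five measurements relative to the reference time (6 weeks, 3 months, 6 months, 12 months and 18 months after randomization"), which leaves baseline as the sixth. The Type 1 text also allows up to six values of y, yet the times it lists all fall after randomization.

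The sample size targets a difference of "four points on the 0 to 100 ThyPRO composite scale". It takes as given that "the standard deviation of ThyPRO-scores (sigma level) was 20 points". The within-participant correlation is set at 0.50. The error rates are fixed by "a power of 80% and a type I error probability (two-sided α level) of 0.05". It assumes five repeated measurements with compound symmetry.

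**The concern.** A participant's own baseline score is usually one of the best predictors of later scores on the same questionnaire. If later scores correlate 0.50 with baseline, part of the between-participant variation in the primary outcome can be removed using data already in hand. Neither reading of the model does this well:

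- If y is post-randomization only, the stated equation does not use the baseline at all.
- If baseline is one of the y values, b is free, so the model estimates an arm difference at t = 0 that randomization makes zero in expectation. The baseline then acts largely as a reference to subtract.

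At stake is precision in the primary comparison. The Discussion says that the sample size makes no allowance for dropout or off-trial selenium use, so the 80% has no reserve. The same models serve the ThyPRO subscales, TPO-Ab, LT4 dosage and the FT3/FT4 ratio, which also have baseline values.

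**Working it through.** **Inputs** (Sample size estimation): σ = 20, ρ = 0.50 with compound symmetry, difference 4, 236 per arm, two-sided 5%. Here m is the number of follow-up scores averaged and r is the correlation of baseline with each follow-up score. Setting r = 0.50 extends the plan's ρ to baseline; lower values of r are my assumption.

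**1. The plan's own figure.** The variance of a participant's mean is V = σ²[1 + (m − 1)ρ]/m. For m = 5, V = 400 × 3/5 = 240. SE = √(2 × 240/236) = 1.426, z = 4/1.426 = 2.805, and power = Φ(2.805 − 1.96) = 80.1%. The required number is 236 per arm. The stated size is thus reproduced with an unadjusted, time-averaged contrast.

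**2. With baseline as a covariate.** The variance becomes V − σ²r².

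| Contrast | r | Variance | SE | Power |
|---|---|---|---|---|
| Mean of 5 scores, unadjusted | – | 240 | 1.426 | 80.1% |
| Mean of 5, adjusted | 0.50 | 240 − 100 = 140 | 1.089 | 95.7% |
| Mean of 5, adjusted | 0.4 | 240 − 64 = 176 | 1.221 | 90.6% |
| Mean of 5, adjusted | 0.3 | 240 − 36 = 204 | 1.315 | 86.0% |
| Mean of 5, adjusted | 0.2 | 240 − 16 = 224 | 1.378 | 82.7% |
| Mean of 4 on-treatment scores, unadjusted | – | 250 | 1.456 | 78.5% |
| Mean of 4, adjusted | 0.50 | 250 − 100 = 150 | 1.127 | 94.4% |
| Mean of 4, adjusted | 0.3 | 250 − 36 = 214 | 1.347 | 84.4% |
| 12-month score, unadjusted | – | 400 | 1.841 | 58.4% |
| 12-month score, adjusted | 0.50 | 400 − 100 = 300 | 1.594 | 70.8% |

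The rows for r below 0.50 keep the correlation among follow-up scores at 0.50. The four-score rows apply if the five measurements that the Discussion credits to the 12-month period include baseline.

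**3. Baseline as a y value, mean change tested.** Follow-up mean minus baseline has variance V + σ²(1 − 2ρ). At ρ = 0.50 the added term is zero, so power stays at 80.1% (five scores) or 78.5% (four). Subtracting the baseline gains nothing.

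**4. Baseline as a y value, slope d tested.** I took generalized least squares on the written equation, ρ = 0.50, with an effect growing linearly to 4 points at 12 months (d = 4/12 = 0.333 per month).

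| Times used | b free | Common mean at t = 0 |
|---|---|---|
| 0 to 12 months | SE 0.137, 68.0% | SE 0.126, 75.4% |
| 0 to 18 months, effect flat after month 12 | SE 0.084, 81.9% | SE 0.932/12 = 0.078, 88.7% |
| 0 to 18 months, same slope continuing | SE 0.084, 97.8% | SE 0.078, 99.0% |

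The gain is about 1 to 7 points for these effect shapes.

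**5. Slope d on post-baseline data only.** The slope is a weighted sum of follow-up scores with weights that add to zero. Under compound symmetry its covariance with baseline is rσ² times that sum, hence zero. A baseline main effect adds nothing.

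**The case against.** The other side has real points.

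- **The equation is not the whole covariate list.** The Discussion promises adjustment for TSH, which is absent from the equation. The equation is a template for all Type 1 outcomes, and a condensed article may leave covariates to fuller documents. This stands: a reader might infer that baseline adjustment has been ruled out, and the article does not say so. But the article fixes a model and names one adjustment, and baseline ThyPRO is in neither.
- **Baseline may already be in the model.** Six ThyPRO values are reachable only by counting it. This also stands, but step 3 shows that it recovers nothing for a mean-change contrast, and step 4 shows a smaller remaining loss for a slope.
- **The tested coefficient is not named.** A reader might infer that the plan gives up 16 points of power outright. The documents do not support that: the figure belongs to the time-averaged contrast with r = 0.50. For other contrasts the loss can be small or nil.
- **r may be lower than 0.50.** Half the participants are to have had LT4 for less than 3 months, and the Discussion expects them to respond to LT4 itself. That could weaken the link between baseline and later scores.
- **Nothing stated is wrong.** This is correct. The unadjusted estimate is unbiased under randomization, and its standard error already reflects chance baseline imbalance.

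**Conclusion.** The point holds as one of efficiency. It is not an error, a bias or a wrong sample size: 236 per arm does give 80% power unadjusted. As stated, the Type 1 and Type 2 models either ignore baseline ThyPRO or use it inefficiently.

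At the plan's SD and size, baseline adjustment of the time-averaged difference would raise power from 80% to about 96% if r is 0.50, and to about 86% if r is 0.3. For the 12-month score alone the rise is from 58% to 71% at r = 0.50. For the slope with baseline as a y value it is about 1 to 7 points, given an effect that grows linearly. For a slope on post-baseline data it is nil.

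These figures rest on compound symmetry and complete data. A higher r would give more, but the documents offer no ground for assuming one. The sponsor should make the change because it costs almost nothing, though the gain cannot be promised at its upper value.

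**What to change.** Before unblinding:

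1. State that the primary contrast is the on-treatment group difference in the ThyPRO composite, either averaged over the on-treatment visits or at 12 months.
2. Estimate it with post-randomization scores as y and baseline ThyPRO as a covariate. Equivalently, keep baseline as a y value and hold both arms to a common mean at t = 0. In the second form, do not simply drop b from the straight-line model, because that would also force the effect to grow linearly from zero. Let the arm effect be free at each visit after baseline.
3. Reconcile Table 2 with the Type 1 text, so that it is clear whether baseline is a covariate or one of the y values.
4. Add the baseline value to the Type 2 model and to the secondary outcomes that have one: ThyPRO subscales, TPO-Ab, LT4 dosage and FT3/FT4 ratio.

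The cost is a few sentences of analysis wording, one degree of freedom per model, and a simple rule for missing baseline scores. The common-mean form keeps participants without a baseline score. No visits, data or participants are added.

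### The time polynomial of the primary ThyPRO model may be set after seeing the two groups' means, and two unranked analyses are assigned to that outcome, so the 5% error rate is not guaranteed

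*Protocol article*

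**What the plan says.** All references are to the protocol article, Statistical analyses.

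- **Default model.** Under Analytical categories, Type 1 is a repeated-measures mixed model. Its mean has an intercept, an intervention term, a linear time term and their product.
- **Permitted change.** "Depending on the mean value structure in the two groups, this model may be enhanced to include a second- or third-degree polynomial". No threshold, test or fit criterion accompanies this. In the same paragraph the covariance fallbacks are listed in a fixed order.
- **Two analyses.** Under Analytical procedures, "one or two of three types of regression analyses will be applied" to each outcome. Table 2 gives the ThyPRO composite, the only primary outcome, categories 1 and 2. Type 2 is a general linear model for a single measure, with no time point named. The Mann-Whitney test is called a sensitivity analysis. Neither Type 1 nor Type 2 is ranked against the other.
- **Level.** "Significance tests will be at the 5% level and two-sided".
- **Blinding.** The Blinding and Data analyses sections have the analysis done with the two groups coded, for example, A and B.
- **Sample size basis.** "a design with five repeated measurements having a compound symmetry covariance structure", leading to the statement that "a sample size of 236 experimental participants and 236 control participants is required".

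**The concern.** The degree of the polynomial determines which hypothesis is tested. At degree 1 the product coefficient is the whole difference in slope. At degree 2 or 3 the same coefficient is only the difference in slope at time zero, and a joint test has two or three degrees of freedom. If the analyst looks at the group means and then picks the degree, the test is chosen with its result partly in view.

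The A/B coding does not prevent this. It hides which arm is which but not how far apart the curves lie, and a two-sided test is indifferent to the labels.

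The clause is likely to be used. The Discussion expects newly diagnosed patients to respond to levothyroxine itself, and Expected participant recruitment plans them as half the sample. The measurements in Table 2 also run to 18 months, six months after the intervention ends. A straight line is an unlikely description of either group.

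At stake is the trial's single primary p-value. With two unranked analyses, it is also unclear which result that p-value belongs to.

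**Working it through.** **1. The plan's own figure.** Inputs from the sample size section: difference 4 ("four points on the 0 to 100 ThyPRO composite scale, corresponding to a small to moderate effect"), SD 20 ("the standard deviation of ThyPRO-scores (sigma level) was 20 points"), correlation 0.50, five measurements, two-sided 0.05, power 80%.

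Variance of a participant's mean over five measurements = 20² × (1 + 4 × 0.5)/5 = 400 × 0.6 = 240, so the SD is 15.49.

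n per group = 2 × (1.960 + 0.842)² × 240/4² = 235.5, rounded up to 236. Power at 236 is 80.1%. The stated figure reproduces, and it is the size for a test of an *average* difference over the measurements.

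**2. Error rate with the degree fixed.** Null simulation with 236 per group, SD 20, correlation 0.50, compound symmetry and complete data, 400,000 trials per setting. For a single test at degree 1, 2 or 3 set in advance, the error is 0.0495 to 0.0506. Any fixed degree holds 5%.

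**3. Error rate with the degree chosen from the data.** Write the group differences in the linear, quadratic and cubic orthogonal contrasts as independent standard normal values z1, z2, z3 under the null. The joint group-by-time test at degree k rejects when z1² + … + zk² exceeds 3.84, 5.99 or 7.81 for k = 1, 2, 3. The protocol states no selection rule, so each rule below is an assumption (2,000,000 draws):

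- Degree from the pooled curve, threshold 1.96: 0.050 throughout.
- Degree raised only if both groups show the curvature, threshold 1.96: 0.033 to 0.052, depending on the true common curvature.
- Degree raised if either group shows it, threshold 1.96: 0.080 with no true curvature, falling to about 0.064 with common quadratic curvature and 0.050 with strong common quadratic and cubic curvature.
- Degree raised on the group-by-quadratic or group-by-cubic contrast, thresholds 1, 1.28, 1.64, 1.96: 0.083, 0.089, 0.091, 0.087.
- Most favourable of the three degrees: 0.092.

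The simulation in step 2, run on the protocol's actual visit times, agrees. It gives 0.087 to 0.088 for choice by group contrast, 0.066 to 0.080 when time and group-by-time terms are tested together to set the degree, and 0.092 to 0.093 for the best of three.

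**4. A different tested quantity.** If the test is the model-based difference at 12 months, choosing the degree by significance of its terms gives only 0.050 to 0.060. Taking the best of three degrees gives 0.065 to 0.088.

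**5. Adding Type 2 as a second route to success.** This is a further assumption, not in the text.

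- Fixed linear model, or Type 2 at 12 months: 0.075 to 0.096. For comparison, two independent 5% tests give 1 − 0.95² = 0.0975.
- Best of three degrees, or Type 2 at 12 months: 0.085 to 0.131.
- Best of three degrees, or Type 2 taken as the average score: 0.138.

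**6. Power of the proposed contrast.** Average over the four post-baseline visits to 12 months, adjusted for baseline:

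- Variance of the average = 400 × (1 + 3 × 0.5)/4 = 250.
- Covariance with baseline = 0.5 × 400 = 200.
- Residual variance = 250 − 200²/400 = 150, so the SD is 12.25.
- Standard error of the difference = √(2 × 150/236) = 1.127.
- 4/1.127 = 3.55, and power = Φ(3.55 − 1.96) = 94%.

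For comparison, one time point alone at 236 per group has about 58% power unadjusted and 71% with baseline adjustment.

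**The case against.** The strongest reply is that the polynomial sentence concerns adequacy of fit. It refers to the structure of the means in the groups and mentions no contrast between them. Curvature is expected in both arms for clinical reasons, so a statistician might simply add a quadratic term when both curves bend. On that reading the error rate stays at about 5% or below. This stands, and it rules out the flat statement that the 5% level is broken. It does not rescue the sentence, which gives no rule confining the choice to the pooled curve or to curvature shared by both groups.

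A reader might also infer that the trial runs a false-positive risk of nearly 14%. The documents do not support that. The figure needs Type 2 to be the average score, whereas the protocol says only that it is a single measure. It also needs a win on either analysis to count, and nowhere does the protocol say so. Two analyses of one outcome do not inflate error by themselves.

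Finally, an analysis plan that is not shown may name the lead analysis and the tested coefficient. That is fair, and the missing ranking alone would be a weak point. The degree clause is different in kind: the protocol states a data-dependent choice rather than leaving a detail out.

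**Conclusion.** The clause is wrong as written and should be fixed. The protocol permits the form of its primary model to depend on the observed means of two separated groups, without a criterion, and attaches a second unranked analysis to the same outcome. The 5% level is therefore not guaranteed.

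The protocol does not determine the size of the departure. For a joint group-by-time test it runs from none, or slight conservatism, to 0.08 to 0.09 under choice by group contrast. The 0.13 to 0.14 region is a worst case under an either-or success rule that is not in the text. All figures assume complete data and compound symmetry.

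The point does not touch the sample size, which reproduces.

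**What to change.** Delete the polynomial sentence for the primary outcome and set the mean structure in advance. The preferred form is baseline score, treatment, visit as a category and treatment-by-visit, with the unstructured covariance already specified. A degree fixed beforehand, or one chosen from pooled means only, would also hold 5%.

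Name one contrast within the 12-month intervention period as the only primary test. The average treatment difference over 6 weeks, 3, 6 and 12 months is a natural choice, because the sample size rests on an average over repeated measurements. Label Type 2 and the 18-month data as supportive for this outcome. Mann-Whitney already has that status.

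The cost is one paragraph of text. Over the four post-baseline visits the mean model has nine parameters (eight treatment-by-visit means and one baseline slope), against four for the linear model and eight for the cubic one. With 472 participants that is negligible. Power for a 4-point average difference is about 94% on the protocol's SD and correlation with complete data, so 236 per group need not change.

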Randomization will be performed centrally by a consultant at the SAS Institute A/S (Copenhagen, Denmark). The allocation sequences will be computer-generated with varying block size, and will be kept unknown to the investigators. Randomization will be stratified by clinical trial site and LT4 treatment duration (<3 months or ≥3 months) and the allocation ratio of intervention and control will be 1:1.

#### **
*Informed consent procedure*
**

Potential participants include all patients with suspected AIT who receive LT4 and are identified at referral or visits to the outpatient clinics or via advertising, as previously described. When AIT is confirmed (serum TPO-Ab ≥ 100 IU/ml, measured within the last 12 months), the patient is invited to an information visit. This visit involves obtaining medical history and written informed consent, blood and urine sampling, and information about trial contact as well as randomization.

#### **
*Concomitant medication or treatment*
**

The trial interventions are given in addition to conventional LT4 treatment. Treatment of the hypothyroidism *per se* will take place at participating clinical trial sites, with LT4 treatment at all clinical trial sites aiming for a serum TSH level within reference ranges, as recommended in local clinical guidelines. Patients are normally followed with blood sampling every 1 to 3 months to adjust LT4 dosage according to TSH levels, as well as visits in the outpatient clinic every 3 to 6 months. Participants in the CATALYST trial will be followed with blood sampling during the trial period, as stated in local clinical guidelines. Participants are advised not to take selenium supplementation in addition to the intervention. A dose of selenium common in multivitamin tablets is, however, allowed and participants are instructed and informed about this upon trial entry, and in the written participant information. The participants’ consumption of additional selenium supplements will be monitored during the trial at specific time points.

#### **
*Monitoring participant adherence to intervention*
**

During the trial, participants self-report their adherence to the intervention at the trial visits (3 months and 12 months after randomization) by stating the number of days a week they take their tablets. Participants will also be instructed to bring remaining tablets and empty containers to the 12 month visit, where they will be counted and registered by an investigator or trial nurse.

#### **

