## Discussion

The data available from previous trials warrant further investigation, since a benefit from selenium supplementation is still unproven in patients with AIT. In previous trials of intervention with selenium in patients with AIT, effect on serum TPO-Ab concentration has been the primary outcome. Intervention durations of 3, 6, 9, and 12 months using different selenium formulations have shown positive effects on serum TPO-Ab concentrations. This trial will be the largest yet, with 472 participants, and the first to measure changes in quality of life, by ThyPRO, as the primary outcome. The sample size estimate does not take dropouts or off-trial use of selenium supplements into account. Plasma selenium concentrations will be measured to assess selenium intake during the trial. Importantly, utilizing the ThyPRO questionnaire will enable us to determine how selenium supplementation may affect specific aspects of thyroid-related quality of life in AIT patients. In assessing quality of life, the effect of levothyroxine alone will be taken into account by adjusting for TSH levels. Choosing a 12-month intervention period allows for a time sequence of five measurements. The 6-month postintervention follow-up period was added to assess sustained effects. This trial will also look into selenium’s mechanisms of action in AIT, by measuring biomarkers of immunological activity, and will be the first to evaluate whether selenium supplementation affects LT4 dosage. Dosage reduction is of clinical interest and discontinuation of LT4 would be of direct clinical relevance. An effect of selenium supplementation on LT4 dosage is conceivable, owing to upregulation of selenoproteins involved in thyroid hormone synthesis or thyrocyte protection.

Participants will be stratified for LT4 treatment duration of more or less than three months, corresponding to newly diagnosed and established patients, respectively. Participants in the newly diagnosed patient group will respond to LT4 treatment *per se*, in terms of restoration of euthyroidism, while the established patient group will not experience major fluctuation in the thyroid hormone levels during the study period. The stratification also allows an investigation of whether the newly diagnosed and established patient groups respond differently to selenium supplementation. This investigation will, however, be strictly exploratory, as it is likely to be underpowered.

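### The first fallback covariance, a spatial power law, has no stable between-patient component, so if it is ever used its model-based tests may have the wrong error rates (minor, conditional)

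*Protocol article*

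**What the plan says.** In the Protocol article, Statistical analyses, Analytical categories, Type 1 outcomes are modelled as y = a + b·I + c·t + d·I·t in a repeated-measures mixed model, with polynomial terms in time if needed. The covariance is unstructured. Only if that fit fails to converge does the fallback rule apply: "the following covariance structures will be tried in the specified order: the spatial power law and the compound symmetric". The rule covers the ThyPRO composite and every other outcome that Table 2 assigns to Type 1.

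Under Primary outcome: sample size estimation, the calculation is "based on a design with five repeated measurements having a compound symmetry covariance structure". Its inputs are a difference of "four points on the 0 to 100 ThyPRO composite scale", and that "the standard deviation of ThyPRO-scores (sigma level) was 20 points". The remaining inputs and the result read "With a correlation between observations on the same participant of 0.50, and a power of 80" per cent and "a type I error probability (two-sided α level) of 0.05, a sample size of 236 experimental participants and 236 control participants is required".

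Table 2 gives the ThyPRO times as baseline, 6 weeks, and 3, 6, 12 and 18 months. The primary outcome is defined over the 12 months of intervention. The article does not say which coefficient or contrast of the model is the primary test.

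**The concern.** A spatial power law has two parameters, a variance and a rate r, and sets the correlation between visits g months apart to r^g. It has no floor. Quality-of-life scores usually contain a lasting patient-level component, and the constant correlation used for sizing is the extreme case of one. When a power law is fitted to such data, the close visits and the distant visits pull r in different directions. The compromise leaves the distant visits looking nearly independent.

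The model then credits repeated scores with more independent information about the level of the arm difference than they hold, so its standard error is too small. It also misses the cancellation of patient effects in within-patient change, so the standard error of the slope is too large. At stake are false positives for a level contrast and lost power for a slope contrast, in exactly the situation where the pre-specified fallback is meant to protect the inference.

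**Working it through.** **Inputs.** From the article: SD 20, correlation 0.50, difference 4, two-sided 5%, 80% power, 236 per arm, "the allocation ratio of intervention and control will be 1:1", and visits at 0, 1.5, 3, 6, 12 and 18 months. No dropout is used in steps 1-4, in line with "The sample size estimate does not take dropouts or off-trial use of selenium supplements into account".

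**Step 1, the plan's own figure.** For a time-averaged difference under compound symmetry with m = 5:

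n = 2(1.96 + 0.842)² × 20² × [1 + (m − 1)ρ]/m ÷ 4² = 2 × 7.85 × 400 × 0.60 ÷ 16 = 235.5, so 236 per arm. The stated figure reproduces.

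**Step 2, what the power law fits.** Take compound symmetry with 0.50 as the truth, and find the power law closest to it in Kullback-Leibler divergence, which is where the fit settles in large samples. With six visits this gives r = 0.740 per month and variance 418. The fitted correlations are 0.740^6 = 0.16 at 6 months, 0.740^12 = 0.03 at 12 months and 0.740^18 = 0.004 at 18 months, against 0.50 throughout.

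**Step 3, error rates.** Fit the linear model by generalised least squares with that covariance. Compare the standard error the model reports with the true one. Type I error = 2[1 − Φ(1.96 × SE_model/SE_true)]. On a straight line, the arm difference at t = 6 is the average over months 0-12.

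| Visits used | Contrast | SE model | SE true | Type I error |
|---|---|---|---|---|
| 0-18 months | t = 6 | 1.106 | 1.422 | 12.7% |
| 0-18 months | month 12 | 1.136 | 1.475 | 13.1% |
| 0-18 months | d | 0.142 | 0.088 | 0.2% |
| 0-12 months | t = 6 | 1.132 | 1.449 | 12.6% |
| 0-12 months | month 12 | 1.757 | 1.762 | 5.1% |
| 0-12 months | d | 0.216 | 0.142 | 0.3% |
| 1.5-12 months | t = 6 | 1.239 | 1.466 | 9.8% |
| 1.5-12 months | d | 0.245 | 0.167 | 0.4% |

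First row: 1.96 × 1.106/1.422 = 1.52, and 2[1 − Φ(1.52)] ≈ 0.127.

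Simulation agrees. Over 1,500 null trials with six visits, error was 11.7% for the 0-12 month mean, 12.5% at month 12 and 0.2% for d. Over 2,000 REML fits with visits at 0-12 months, it was 11.8% for the average over visits, 4.9% at month 12 and 0.6% for d.

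On the secondary-outcome schedule (0, 3, 12 and 18 months), the same truth gives 8.0% at t = 6, 8.4% at month 12 and 0.4% for d.

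**Step 4, other truths.** These correlation patterns are assumptions; the article reports none beyond 0.50.

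- Mixed (stable part 0.4, part 0.4 decaying at 0.85 per month, noise 0.2; six visits): the power law gives 8.8% at t = 6, 9.1% at month 12 and 0.9% for d.
- True power-law decay: the power law gives 5.0% for every contrast.
- True power-law decay at 0.90 per month, analysed with compound symmetry and model-based standard errors: d has 19% error (0-12 months) to 22% (0-18 months).
- Power law plus random participant intercept: about 5-7% for every contrast under the constant, mixed and decaying truths.

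**Step 5, the trigger.** An unstructured 6 × 6 matrix has 6 × 7/2 = 21 parameters for 472 participants. In 100 simulated trials with an assumed 30% dropout and 5% intermittent missingness, none failed to converge. That check used an EM algorithm, not the SAS procedure, and one outcome.

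**The case against.** A reader might infer that the fallback contradicts the sample size. It does not. Compound symmetry is a planning assumption. The specified analysis is unstructured, which contains compound symmetry as a special case, and compound symmetry is itself the second fallback. Planning with a simple structure and analysing with a general one is normal practice.

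A reader might also infer that the primary test has the wrong error rate. That too goes beyond the documents. The distortion needs two things together: failure of the unstructured fit, and a correlation with a stable component. It also depends on the contrast, which the article does not name. At month 12 without the 18-month score the error is 5.1%, and the 13% figure needs a post-intervention visit although the primary outcome is defined over 12 months. Because r is estimated, near-zero correlation at long gaps is not built in: at 0.95 per month it would be 0.95^12 = 0.54 at 12 months.

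The power law also has a real merit here. It uses the actual, unequal gaps between visits, and simply swapping the order would exchange one weakness for another (step 4). Finally, the choice of standard-error estimator is commonly left to the analysis plan, so silence on it is not an error. That the power law converges so readily that compound symmetry would rarely be reached is plausible but untested.

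All of this limits the point. What stands is that the stated first fallback cannot represent a stable patient effect, and that a modest change gives close to nominal error under each pattern tried.

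**Conclusion.** This is a conditional weakness in a stated fallback rule, of minor priority. If the unstructured fit fails and within-patient correlation is constant at 0.50, model-based tests under the power law have type I error of about 10-13% for the arm difference at t = 6. At month 12 the error is about 13% with the 18-month score and about 5% without it. For d it is about 0.2-0.4%. A partly stable correlation gives smaller distortions in the same directions; purely decaying correlation gives none. The figures assume the linear mean model, 236 per arm, complete data and no robust standard errors. The 236 per arm and the unstructured main analysis are unaffected.

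**What to change.** Keep the unstructured matrix as the main analysis. Replace the fallback sequence with:

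1. a spatial power structure plus a random participant intercept;
2. compound symmetry.

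Use empirical (sandwich) standard errors whenever the covariance is not unstructured.

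Do not simply move compound symmetry or Toeplitz to the front with model-based standard errors. Compound symmetry inflates the slope test when correlation decays. Toeplitz goes by visit order, so it would give the 6-week gap after baseline and the 6-month gap before month 12 the same correlation.

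The cost is a wording change in the analysis section and small additions to the mixed-model call. The random intercept adds one parameter, and its variance may be estimated as zero if correlation purely decays. Sandwich standard errors are slightly less efficient, which is negligible with 236 per arm.
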